### Sample size and power calculation

Exploratory analysis of HES data suggests that approximately 9.5% of children born to first-time teenage mothers are admitted to hospital for injuries by age 6. Assuming a baseline rate of 9.5% for the percentage of children with this outcome up to age 6, a total of 6798 children (3399 in each group) would be required to observe a significant relative reduction of 20% in hospital admissions for injuries, with 80% power and a 5% significance level. In our cohort, birth outcomes will be available for around 31 000 FNP births; 24 000 FNP families will have a full 3 years of follow-up and 9000 will have a full 6 years of follow-up. The number of control (never enrolled) families will vary for the propensity score and adjusted analyses; up to one million potential controls (corresponding to total births to women aged 13–24 between April 2010 and March 2017) will be available for these analyses.

Key Stage 4 and 5 assessment outcomes (for ages 14–16 and 16–18, respectively) will be examined among mothers who have not sat these examinations before giving birth. We estimate that the sample size for this subgroup will be around 1800 FNP mothers for Key Stage 4 and 13 000 for Key Stage 5.

### Analysis

We will describe maternal sociodemographic characteristics at the time of pregnancy, previous health and educational characteristics and pregnancy outcomes for our retrospective cohort of teenage and young mothers (described above).

To determine whether the teenage mothers most in need receive FNP (objective 1), we will identify the proportion of eligible families participating in FNP by LA and over time. Predictors of participation will be derived from HES and NPD data. Since recruiting practices vary locally, we will compare data from high-coverage and low-coverage LAs, to explore whether FNP families in low-coverage LAs are more highly selected than those within LAs offering the programme to more mothers (eg, it may be hypothesised that nurses in some areas may target the most advantaged mothers or use a first-come-first-served model in others).

To examine the effects of the FNP (objective 2), we will compare outcomes for mothers ever enrolled in FNP, and their children, versus those never enrolled, using two analysis strategies to account for measured confounders related to FNP participation and outcomes. Propensity score matching aims to minimise bias, while adjustment for confounders aims to minimise variance.

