## Introduction

Approximately 3% of babies each year (19 000 in 2018) are born to mothers aged below 20 in England and Wales.^1^ Teenage mothers are more likely to experience adversity and have rapid repeat pregnancies, and are less likely to be engaged with education and employment compared with older mothers.^2–5^ For their children, young maternal age is associated with higher incidence of preterm birth and low birth weight^6 7^ and a greater risk of child maltreatment and associated adverse long-term consequences including poorer physical, social, emotional and cognitive outcomes.^8–10^ These adverse maternal and child outcomes of teenage pregnancy, due to social adversity, disruption to education and employment, and child-rearing practices, are of major importance to public health research.^11 12^

The Family Nurse Partnership (FNP) is an intensive home visiting programme that aims to improve outcomes of pregnancies among vulnerable young mothers. Participants receive up to 64 home visits from early pregnancy until the child’s second birthday. Specifically, the FNP aims to improve birth outcomes, optimise child health and development and promote economic self-sufficiency among vulnerable mothers.^13^ Three randomised controlled trials in the USA found evidence of benefit on a number of maternal and child outcomes, including reductions in child maltreatment, child emergency department visits and subsequent births, as well as some improvements in child developmental outcomes and longer subsequent birth intervals.^14–18^ Effects on hospital visits for injury or maltreatment, children’s educational achievements and maternal educational qualifications were less consistent. A trial in the Netherlands found reduced child maltreatment reports by age 2,^19^ and a trial of a FNP-based model in Germany reported improved child development among high-risk women only, although no difference in subsequent births within 2 years.^20^ Non-randomised studies have reported reduced child maltreatment,^21^ infant death^22^ and subsequent births^23^ among FNP participants compared with controls, as well as different patterns of emergency room visits.^24^

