## Methods and analysis

### Study design and population

This study aims to evaluate the real-world, ongoing implementation of the FNP in England on the outcomes of mothers participating in FNP and their children, with the specific objectives of assessing (1) which groups of mothers receive FNP across LAs, (2) the effect of the FNP on maternal and child outcomes, including which families benefit most from FNP and (3) contextual factors influencing FNP programme effect. It will complement results from the Building Blocks trial in England,^27^ Building Blocks 2–6 year follow-up^31^ and evaluation of the FNP in Scotland using linked administrative data.^37^

We will create a retrospective cohort of all first-time mothers aged 13–24 years giving birth in England between 1 April 2010 and 31 March 2017 and their children, using individual-level, linked, longitudinal data from routinely collected hospital, education and social care records. Mothers up to 24 years will be included because some FNP sites modified inclusion criteria to include young mothers up to this age. The cohort will be created through linkage of hospital records (Hospital Episode Statistics (HES)), education and social care records (National Pupil Database (NPD)) and FNP programme data for mothers and their children. Our approach builds on previous linkage of education and health records and validated methods of linking hospital records for mothers and babies.^38 39^ The infrastructure and methodology used to create the linked database will be highly relevant for ongoing evaluation and monitoring of the FNP and other early interventions.

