#### Programme delivery: FNP Information System (FNP IS)

The HES cohort will be linked to the FNP IS to obtain information on participation in FNP. The FNP IS is a bespoke system that supports the implementation of the FNP programme in England, provided by NHS Digital under contract to the FNP National Unit on behalf of Public Health England. Data are reported in real time and are used locally by FNP teams and nationally by the FNP National Unit to monitor programme delivery and support quality improvement.

Data collected in the FNP IS include information from the mother and child collected at enrolment (by 28 weeks gestation at the latest, including mother’s age, marital status, living arrangements, education, employment, social care), 36 weeks gestation (including maternal health, alcohol, drugs and smoking), birth (including birth weight and gestational age) and at regular intervals until 24 months after birth (including child health and development, social care and other maternal baseline variables). Information on each visit is also collected (including date, length of visit, family nurse seen and referrals to other services). The FNP IS became functional in 2009, and data quality is reported to be high from 2010 onwards. FNP data have been used in previous research.^48 49^

FNP IS contains maternal and child identifiers at enrolment/birth: name, sex, date of birth, postcode, GP code and NHS number. When mothers graduate from the FNP, pseudonymised data are retained by the FNP National Unit only and identifiers are held solely on secure servers at NHS Digital. Since some identifiers might have changed since enrolment (eg, mother’s name, postcode), identifiers will first be updated using the Personal Demographic Service (PDS) within NHS Digital, so that the most relevant set of identifiers can be used for linkage.^50^

The time span covered by each data source (including look-back, study and follow-up periods) is described in the online supplementary appendix.

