Some healthcare use outcomes—A&E visits and unplanned hospital admissions for any diagnosis—will be reported as descriptive outcomes, since the direction of effect could be interpreted positively or negatively (FNP participation might reduce the need for emergency care or alternatively increase appropriate care-seeking). Nonetheless, they represent important outcomes for understanding the effects of FNP on care-seeking behaviour. Similarly, the potential for surveillance bias to distort the effect of early life interventions on child maltreatment has been discussed extensively:^19 27 53^ indeed, nurse home visiting results in increased contact with nurses, potentially leading to lower thresholds for reporting among participating families than control group families. This bias in ascertainment of maltreatment may dilute or reverse the association between FNP participation and maltreatment. Conversely, it has also been hypothesised that nurse’s closeness to participants may delay reporting of suspected maltreatment.^19^

Maternal outcomes will include unplanned hospital admissions for adversity-related reasons (violence, self-harm and drug/alcohol abuse) after birth and death. As for children, maternal rates of A&E visits and unplanned hospitalisations will be reported as descriptive outcomes. We will also examine the effect of FNP participation on school attendance and achievement after birth, and subsequent pregnancies within 18 months of the first birth ending in live or stillbirths. We will examine subsequent births from a pregnancy within 18 months (rather than 24 months as measured in the Building Blocks trial) because 18-month birth-to-pregnancy intervals are associated with the highest risks of adverse outcomes for women and babies.^54^ However, in addition to the outcomes in table 1, we will validate our findings against the outcomes reported in the Building Blocks trial by examining a range of birth outcomes and subsequent deliveries from pregnancies within 24 months of the index birth.

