#### Propensity score matching

To derive propensity scores, we will construct logistic regression models with FNP participation as the outcome, including as predictors all available maternal characteristics up to 28 weeks gestation (at which point the vast majority of mothers have been enrolled), including looked after status, educational achievement and pre-pregnancy chronic conditions. Matched groups will be formed by matching FNP participants to eligible non-participants with a similar participation propensity score.^55^ Effects will be estimated as the difference in outcomes between matched groups. Multiple imputation will be used to account for missing data where data are expected to be missing at random.^56^

The main analysis will restrict matching within the same LA^57^ and time period in which FNP was offered within that LA. Secondary analyses aiming to achieve more closely matched groups (with potentially smaller numbers) will match, first, within the same LA but in different time periods, comparing outcomes for eligible families before versus after FNP was offered; and second, within the same time period but in different LAs, comparing outcomes for eligible families in LAs that did and did not offer FNP.

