### Limitations

We do not have individual-level data on primary care or the number of visits from health visitors that families receive outside of FNP; however, we will seek local aggregate data on usual care models of health visiting and targeted support for teenage mothers over time to examine how these differed across LAs.

Data on mothers who were offered FNP but declined are not routinely collected. Women who refuse participation may therefore be included in our control group; this may introduce some selection bias, since refusers are likely to differ from FNP accepters in ways that also affect their outcomes. However, propensity score matching sensitivity analyses will restrict controls to women who could not have been offered FNP (either before FNP was offered or in LAs not offering FNP). In the event of remaining unmeasured confounders, grouping refusers with other non-participants may result in an underestimation of FNP effects (if less vulnerable women are more likely to refuse) or overestimation (if more vulnerable women are more likely to refuse). Although individual-level data on refusers are not available, we will obtain data from FNP sites, where available, on the rate and aggregate characteristics of mothers declining participation.

FNP eligibility criteria require enrolment before 28 weeks gestation. Due to a high proportion of missing data on gestational age at first antenatal booking appointment, we will include women who are missing this information as potential controls. Ninety-two per cent of all women present by 20 weeks gestation;^63^ therefore, any resulting bias in results is likely to be small. However, we will also conduct sensitivity analyses restricting the control group to women presenting up to 28 weeks at booking appointment, to match FNP eligibility criteria.

We estimate at least 90% completeness for linkage of HES and NPD. There may be selection bias in the analyses related to education and social care outcomes due to mothers or children who are not linked being different to those whose records are successfully linked.^51^ Nonetheless, data completeness in our cohort is likely to be substantially higher than follow-up rates for medium-term outcomes in most existing trials^15 64 65^ (although the Building Blocks trial in England is also using linkage of routine records for follow-up to the child’s seventh birthday).^31^ Linkage of mother-baby records within HES is high (98%).^38^

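### The ever versus never enrolled comparison has no gestational time zero, so births before enrolment can fall only among controls, tilting child death and the birth outcomes towards FNP

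*Protocol article*

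**What the plan says.** Study design and population defines the cohort by delivery: "all first-time mothers aged 13–24 years giving birth in England between 1 April 2010 and 31 March 2017". No minimum gestation is given. Under Analysis, exposure is classified over the whole pregnancy: "we will compare outcomes for mothers ever enrolled in FNP, and their children, versus those never enrolled".

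Enrolment happens during pregnancy. The FNP Information System section describes data "collected at enrolment (by 28 weeks gestation at the latest"; the Propensity score matching section is slightly looser, using "all available maternal characteristics up to 28 weeks gestation (at which point the vast majority of mothers have been enrolled"). No distribution of enrolment week is given.

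Matched groups come from "matching FNP participants to eligible non-participants with a similar participation propensity score". The main match is within local authority and period. Secondary matches take controls from another period or another authority. The adjusted analysis conditions on maternal characteristics before enrolment.

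The one restriction on controls tied to gestation is a sensitivity analysis in Limitations, "restricting the control group to women presenting up to 28 weeks at booking appointment".

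Child death from 0 to 7 years is listed in Table 1. Birth outcomes are not in Table 1. They serve to check the cohort against the Building Blocks trial, "by examining a range of birth outcomes and subsequent deliveries from pregnancies within 24 months of the index birth" (Outcomes of interest).

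**The concern.** Take a woman who would have enrolled at 26 weeks but gives birth at 25. Her delivery is in the cohort and she was never enrolled, so she is a control. The same birth cannot appear on the FNP side. The time from the start of pregnancy to enrolment is therefore event-free by construction for participants, which is immortal time bias.

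Nothing stated removes it:

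- **Eligibility.** She was eligible until she delivered.
- **Maternal covariates.** The imbalance comes from how exposure is assigned, not from who the mothers are. The planned analysis of unmeasured confounding addresses a different problem.
- **Booking restriction.** It removes women who present late, not women who deliver early.
- **Secondary matches.** Participants must still have reached enrolment; the controls from other periods or authorities need not have.

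The study is presented as able to detect small differences and differences in rare outcomes. A small systematic tilt in child death could be read as benefit, and a tilt in birth outcomes could make agreement or disagreement with the trial misleading.

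**Working it through.** **The plan's own figure.** The sample size is for injury admissions: 9.5% against 9.5% × 0.8 = 7.6%, two-sided 5%, 80% power. With pooled variance and mean proportion 0.0855,

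n = [1.96 √(2 × 0.0855 × 0.9145) + 0.842 √(0.095 × 0.905 + 0.076 × 0.924)]² / 0.019² = 3399 per group, 6798 in total.

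This matches the article and does not depend on the point made here.

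**Null model for child death (no programme effect, no confounding).** All inputs are assumptions, because the document gives none of them:

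- f, share of births at 22 to 27 completed weeks: 0.4 to 0.8%
- m, mortality among those births: 30 to 50%
- d, mortality among all other births: 0.3 to 0.4%
- c, share of eligible mothers who would enrol: 5 to 25%
- enrolment gestation: normal, mean 16 to 22 weeks, SD 4 to 5, truncated to 5 to 28 weeks
- early births spread evenly over 22 to 28 weeks

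**Step 1.** Let q be the share of would-be participants' early births that precede enrolment: 1 minus the average, over 22 to 28 weeks, of the cumulative enrolment distribution.

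**Step 2.** Risk of death in each group:

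- FNP: r1 = [f(1−q)m + (1−f)d] / [f(1−q) + (1−f)]
- Controls: with e = (1−c)f + cfq and o = (1−c)(1−f), r0 = (em + od) / (e + o)

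**Step 3.** Results over the full range of f, m, d and c:

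| Mean enrolment (weeks) | q, SD 4 | q, SD 5 | Null death RR |
|---|---|---|---|
| 16 | 1.8% | 3.7% | 0.972–0.996 |
| 18 | 4.8% | 7.2% | 0.946–0.988 |
| 20 | 10.6% | 12.5% | 0.908–0.975 |
| 22 | 19.3% | 19.3% | 0.860–0.954 |

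- **Mildest** (f 0.4%, m 30%, d 0.4%, c 5%, q 1.8%): r1 = 0.516%, r0 = 0.519%, RR 0.996.
- **Middle** (f 0.6%, m 40%, d 0.4%, c 5%, q 10.6%): r1 = 0.613%, r0 = 0.639%, RR 0.959.
- **Strongest** (f 0.8%, m 50%, d 0.3%, c 25%, q 19.3%): r1 = 0.621%, r0 = 0.723%, RR 0.860.

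**Step 4. Secondary matches.** Controls who could not have enrolled correspond to c = 0. In the middle case r0 = 0.006 × 0.40 + 0.994 × 0.004 = 0.638%, so RR = 0.613/0.638 = 0.961. Most of the tilt remains.

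**Step 5. Birth weight**, assuming a 2400 g gap between early and other births. The shift is 2400 g times the difference in early-birth share. Mildest: (0.4004% − 0.3928%) × 2400 = 0.2 g. Strongest: (0.851% − 0.647%) × 2400 = 4.9 g.

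**Sensitivity to the model.** With early births only at 24 to 27 weeks (0.3 to 0.7% of births), the null death RR is 0.995–0.999 for enrolment centred at 16 weeks (SD 4), 0.96–0.99 at 20 weeks (SD 4) and 0.87–0.96 at 24 weeks (SD 3). If everyone enrolled at 28 weeks, an extreme bound, it would be 0.39–0.81. The direction favours FNP in every case.

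**The case against.** **The article condenses a plan.** It promises a detailed statistical plan, and how eligibility is applied to controls is commonly left to one. Control characteristics are also taken up to 28 weeks, which hints at a reference point. This stands in part: a later plan could add the condition. But the contrast and the control definition are fixed here without it, and a plan that follows them would carry the bias forward.

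**The size is assumed and may be small.** This stands. The Introduction says "Participants receive up to 64 home visits from early pregnancy", which points towards early enrolment. If early births rise linearly with gestation instead of being spread evenly, q falls to about 1 to 14%, and with c = 0 the strongest RR moves from 0.89 to about 0.92. With f = 0.6%, m = 40% and d = 0.35%, 31 000 FNP births give 31 000 × (0.0024 + 0.00348) ≈ 182 deaths. The standard error of the log RR is then about 1/√182 = 0.07 with unlimited controls and √(2/182) = 0.10 with 1:1 matching. A bias of 1 to 4% lies within that.

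**Few outcomes are touched.** This also stands. The abstract names early development, injury or maltreatment admissions and children in care, and no bias is shown for these. Birth outcomes serve validation only, and the birth outcome named for the trial is birth weight, where the shift is a few grams.

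**A 28-week restriction is not a free remedy.** This stands too. It removes participants' own births between enrolment and 28 weeks, so it cannot serve as the main analysis without losing any programme effect there.

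**Conclusion.** The point holds for child death and the birth outcomes. The asymmetry and its direction follow from the stated cohort, exposure and control definitions. Its size does not: a null death RR of about 0.86 to 0.996 rests wholly on the assumptions listed, is negligible if most women enrol early, and is material only if many enrol late. The actual enrolment-week distribution would settle this.

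Three stronger readings are tempting and are not supported. A reader might infer that the whole evaluation is biased; no effect on injury admissions, education, social care or the sample size has been shown. A reader might infer that all pregnancies ending before enrolment become controls; only recorded births enter the cohort, so earlier losses are in neither group. A reader might infer that very preterm birth or length of stay is a distorted study outcome; the article names neither.

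**What to change.** For child death and the birth outcomes, define time zero as gestation at enrolment:

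- **Matched analyses, including the secondary matches, and the Building Blocks replication:** require each control to be still pregnant at the matched participant's gestation at enrolment.
- **Adjusted analysis:** align time zero in the same way, comparing women who enrol at a given gestation with women still pregnant at that gestation.
- **Sensitivity analysis:** restrict both groups to births at 28 or more weeks, stating that it cannot capture any programme effect on births before 28 weeks.
- **Reporting:** give the distribution of gestation at enrolment.

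The article lists gestational age among the data collected at birth but does not say that gestation at enrolment is recorded. It would have to be derived from enrolment date, birth date and gestational age at birth, if these are available.

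The cost is one matching condition, a rule for missing gestational age and a small loss of controls. If controls must also remain never enrolled, a smaller residual stays, because women who enrol later leave the control pool while those who deliver first remain. It inflates the controls' early-birth share by at most about cq/(1−c) in relative terms: 0.05 × 0.106/0.95 = 0.6% in the middle case and 0.25 × 0.193/0.75 = 6.4% in the strongest. The 28-week analysis avoids this as long as enrolment is complete by then, so the two should be read together.

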#### Propensity score matching

To derive propensity scores, we will construct logistic regression models with FNP participation as the outcome, including as predictors all available maternal characteristics up to 28 weeks gestation (at which point the vast majority of mothers have been enrolled), including looked after status, educational achievement and pre-pregnancy chronic conditions. Matched groups will be formed by matching FNP participants to eligible non-participants with a similar participation propensity score.^55^ Effects will be estimated as the difference in outcomes between matched groups. Multiple imputation will be used to account for missing data where data are expected to be missing at random.^56^

The main analysis will restrict matching within the same LA^57^ and time period in which FNP was offered within that LA. Secondary analyses aiming to achieve more closely matched groups (with potentially smaller numbers) will match, first, within the same LA but in different time periods, comparing outcomes for eligible families before versus after FNP was offered; and second, within the same time period but in different LAs, comparing outcomes for eligible families in LAs that did and did not offer FNP.

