#### Education and social care records: National Pupil Database (NPD)

The HES cohort of mother-baby pairs will be linked to education and social care records from the Department for Education for both mothers and children in the FNP and control groups (including information before delivery for mothers). Information on assessments, attainment and progression at each key stage is available for all pupils in state schools in England, alongside eligibility for free school meals, information about special educational needs and information about absences and exclusions. NPD data, including social care data, have been used extensively in research.^43^

For both mothers and their children in the cohort, we will link HES data to the following NPD databases:

The yearly School Census (formerly PLASC), the Pupil Referral Unit (PRU) Census and Alternative Provision—including pupil-level information from 2002 for pupils aged 2–19+ on special educational needs, free school meal eligibility and information about absences and exclusions.The Children in Need Census (CINC)—including information on referrals to children’s social services, assessments carried out on these children and whether the children became the subject of a child protection plan, from 2008.^44^The Children Looked After (CLA) return—including information on all looked after children and recent care leavers in England, from 2005.^45 46^

For mothers only, we will link to Key Stages 2, 4 and 5 data, which includes teacher assessments and/or test results in Years 3–6 (ages 7–11), Year 11 (age 16) and Year 12/13 (ages 17–18). For children only, we will link to the Early Years Census and Early Years Foundation Stage Profile (EYFSP), including teacher assessments for 3 and 4 year olds (from 2008) and 2 year olds (from 2014), as well as to Key Stage 1 assessment data (ages 5–6).

A Unique Pupil Number (UPN) is used for linkage of CLA and CINC with the NPD. The UPN is usually assigned at first entry to a maintained school or nursery, typically around the age of four or five. Therefore, it is not possible to link the NPD to CLA data for children who are looked after only before they enter nursery/school or adopted children (who are provided with a new UPN).^47^ However, information on out-of-home care available for FNP participants at all ages will enable us to examine the scale of underestimation of out-of-home care before school in the administrative data.

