#### Adjusted analyses

This analysis will be an unmatched comparison, adjusting for maternal characteristics prior to enrolment for each outcome based on causal diagrams and hypothesised influence on effect estimates.

Sensitivity analyses will determine the strength of unmeasured confounding required to invalidate results.^58 59^ To further assess the robustness of findings to the analysis approach and to evaluate any potential differences in results due to the use of real-world data, we will use our cohort to replicate findings observed in the Building Blocks trial. For each analysis strategy, we will derive trial outcomes for a group of families in the administrative data cohort with the same aggregate baseline characteristics as trial participants.

Stratified analyses and interaction terms will be used to investigate effect modification according to the maternal characteristics in box 1, based on previous evidence suggesting the youngest and most disadvantaged mothers are most likely to benefit from the FNP.

Box 1Maternal characteristics prior to enrolment (Family Nurse Partnership participants) or up to 28 weeks gestation (controls) potentially producing effect modificationMaternal age at enrolment.Ethnicity.Healthcare use prior to enrolment (unplanned admissions and A&E visits, admissions for drug/alcohol abuse, violence or self-harm).^69^Chronic conditions (including mental health conditions captured in hospital data).^70^Educational achievement.Special educational needs.Eligibility for free school meals.Out-of-home care.Area-level deprivation.

To identify contextual factors associated with benefitting from FNP (objective 3), we will explore individual and programme characteristics associated with programme engagement, including maternal characteristics prior to enrolment, nurse characteristics and usual care models in LAs. We will also investigate any differences in FNP effect between LAs and between our cohort and the corresponding Building Blocks trial population (restricted to trial inclusion criteria), to help generalise trial results.

A detailed statistical plan will be written prior to analyses. Statistical models will take into account clustering within LAs, and also among nurses where appropriate. Data will be analysed in Stata. Study results will be reported in accordance with GUILD, STROBE and RECORD guidelines.^60–62^

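### The matched effect is a difference between matched groups with no outcome model, so any measured imbalance left by the within-area match would pass into the estimate, chiefly for maternal outcomes

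*Protocol article*

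**What the plan says.** Under Propensity score matching, the article fits a logistic model for FNP participation, "including as predictors all available maternal characteristics up to 28 weeks gestation", "including looked after status, educational achievement and pre-pregnancy chronic conditions". Participants are then matched to eligible non-participants with a similar score, and "Effects will be estimated as the difference in outcomes between matched groups". No covariate term is attached to that effect step.

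The main match is within the same LA and within the period when FNP was on offer there. Of the alternatives the article says: "Secondary analyses aiming to achieve more closely matched groups (with potentially smaller numbers) will match, first, within the same LA but in different time periods", and then within the same period but across LAs.

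The Analysis section explains why there are two strategies: "Propensity score matching aims to minimise bias, while adjustment for confounders aims to minimise variance". Under Adjusted analyses, the second strategy is an unmatched comparison with covariates chosen for each outcome from causal diagrams. The same section says that models will allow for clustering and that a detailed statistical plan will follow.

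Some maternal outcomes have a direct baseline in the linked data. The NPD section says "For mothers only, we will link to Key Stages 2, 4 and 5 data", and Key Stages 4 and 5 are themselves outcomes in Table 1. Box 1 lists "Healthcare use prior to enrolment (unplanned admissions and A&E visits, admissions for drug/alcohol abuse, violence or self-harm"), and Table 1 has maternal admissions of the same types after birth.

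**The concern.** The article treats matching and covariate adjustment as alternatives with different aims. They can be combined: a regression fitted in the matched sample keeps the matched comparison and also removes measured imbalance that the match leaves.

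Matching on a single score balances each covariate only on average, and only where close controls exist. Restricting the match to one LA and one period shrinks the local pool. The article's own remark that the secondary matches aim at closer groups implies that the main match may be less close.

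The unmatched adjusted analysis does not repair this. As described, it does not impose the same-LA, same-period restriction that defines the main matched comparison. If imbalance remains in a strong predictor such as prior attainment, it passes into the matched estimate in proportion to that predictor's correlation with the outcome.

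**Working it through.** **1. The plan's own figure.** Inputs from Sample size and power calculation: 9.5% versus 7.6% (a 20% relative reduction), 5% significance, 80% power. Sidedness is not stated; two-sided is taken. With pooled variance and mean proportion 0.0855:

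n = [1.960 × √(2 × 0.0855 × 0.9145) + 0.8416 × √(0.095 × 0.905 + 0.076 × 0.924)]² / 0.019² = (0.7751 + 0.3326)² / 0.000361 ≈ 3399 per group, 6798 in total.

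This matches the article. It is an unadjusted two-proportion calculation.

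**2. How thin the local cells are.** The article gives about 1800 FNP mothers for Key Stage 4 and more than 130 LAs. 1800 / 130 ≈ 14 per LA at most on average, and over the seven birth years 14 / 7 ≈ 2 per LA-year. The number of eligible never-enrolled mothers per LA at that age is not given, so the control ratio below is assumed.

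**3. Imbalance and bias, within-LA matching (simulation).** Assumptions: 130 LAs, 1800 participants, the baseline included in the propensity score, 1:1 matching within LA, correlation of baseline with outcome 0.5, and no true effect.
- No caliper, 2-3 local controls per participant: the residual baseline difference is 0.07-0.23 SD. Bias = residual difference × correlation, so 0.07 × 0.5 = 0.035 and 0.23 × 0.5 = 0.115, that is about 0.03-0.12 SD. The plain difference rejected the true null in 15%-95% of runs, against 3%-12% for the adjusted matched estimate.
- Cross-check by formula: SE = √(2/1800) = 0.0333 SD. Bias/SE is 1.05 and 3.45. Rejection = Φ(−1.96 + bias/SE) + Φ(−1.96 − bias/SE) = 18% and 93%, in line with the simulated range.
- With 10 local controls per participant, or with a caliper of 0.2 SD of the score's logit, the imbalance is about zero.
- The caliper has a price. Over a wider grid (2-10 controls, one or seven periods) it left 5%-73% of participants unmatched.

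**4. Imbalance without the LA restriction.** With about 1670 participants, roughly 11 potential controls each and a caliper, a baseline difference of about −0.48 SD before matching fell to 0.00 on average afterwards (mean absolute value 0.012-0.014). Bias of the plain difference was about zero.

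**5. Precision.** The textbook factor √(1 − R²) is an upper bound here.
- Key Stage 4, 1800 per group: the detectable difference at 80% power is 2.80 × 0.0333 = 0.093 SD. With R² of 0.25-0.50 (assumed) it would be 0.081-0.066 SD.
- In the matched data of step 4 the ratio of adjusted to plain SE was only 0.91-0.99 for a continuous outcome and 1.00 for a binary outcome near 9.5%.
- For child injury admissions, R² of 0.01-0.10 would lower 3399 per group to 3365-3059. Power at the 9000 families with six years of follow-up is already 99.5% unadjusted.

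**The case against.** The strongest reply is that this reads much into one condensed sentence. The article never calls the difference unadjusted, it speaks of statistical models with clustering, and it defers detail to a later plan. That has weight. But the article does more than omit a detail: it states the estimator, assigns bias to matching and variance to adjustment, and describes the adjusted analysis as unmatched. A later plan that follows this text would contain no outcome model in the matched sample.

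A reader might infer that prior attainment and prior admissions are ignored in the matched analysis. They are not. Educational achievement is a named propensity predictor, and prior admissions fall under all available characteristics. They are absent only from the effect step.

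A reader might also infer that the main estimate is biased. The documents do not show this, because it depends on caliper and local pool, neither of which is given. Assuming a fixed residual difference of 0.05-0.10 SD gives false-positive rates of 12%-32% at 1800 per group and 52%-98% at 13 000, but that presupposes systematic imbalance in a matched variable. Chance imbalance is already in the standard error. Controls are plentiful overall: one million against 31 000 is about 32 to 1, although that counts all births to women aged 13-24 and not the youngest mothers in a given LA.

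Two further points stand. The outcomes named in the abstract are child outcomes, which have no pre-enrolment baseline of their own. The secondary matches also serve to exclude women who declined FNP, and an outcome model on measured covariates does nothing for that unmeasured selection.

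**Conclusion.** The point holds in a conditional form. As written, the matched estimate has no protection against measured imbalance that survives a same-LA, same-period match. Where local controls are few and no caliper is used, the bias could be about 0.03-0.12 SD; otherwise it is about zero. These sizes rest on an assumed correlation of 0.5, an assumed 2-3 local controls per participant and a correctly specified outcome model, so the protection shown is a best case.

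The case for change is protection against bias, not power: the gain in standard error is about 1%-9% for continuous outcomes and negligible for child injury admissions. It is worth acting on for maternal Key Stage 4/5 and maternal admissions. For child outcomes it is a minor refinement.

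**What to change.** In the statistical plan, state that matched effects will be estimated from an outcome regression fitted in the matched sample, with standard errors clustered on matched set and LA. The model should contain FNP enrolment, the key prognostic characteristics already in the propensity score and, for maternal outcomes, the baseline of the same outcome: Key Stage 2 for Key Stage 4/5, and prior admissions of the same type for maternal admissions. Report a covariate-standardised risk or mean difference, with the plain matched difference beside it. Reword the Analysis section so that matching and adjustment are no longer presented as serving separate aims.

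The cost is a few lines of wording and Stata code, settled before outcomes are analysed. The covariates are already to be linked, and missing values are already to be imputed where missingness at random is plausible. The one drawback is that rare outcomes will need a short covariate list.
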